### Data collection

There are four primary data sources that will be used to collect outcome and key covariate indicators: administrative census data, CHW phone surveys and shadowing, community surveys, and administrative participation data; each of these are discussed below.

#### Administrative census data

A census of all households with pregnant women and children aged 0–5 years was conducted in January 2021 ahead of study activities by U-PNNC as part of the standard MCH&N activities. The census will be used to a) understand underlying characteristics of the study communities and b) identify households with age-eligible children for participation. Households with age-eligible children were given a unique ID and additional information will be gathered including community location, maternal education, number of children 0–5 years old, number of pregnant women and a measure of household wealth.

#### Monthly CHW surveys and shadowing

Phone surveys will be conducted at baseline and monthly with 150 CHWs (two for each of the 75 study communities) by trained enumerators. In addition to the phone/in person monthly survey, enumerators will record all the activities and time spent by CHW on key work activities, including different aspects of the ECD sessions (if in the treatment arms) during shadowing sessions. Originally planned to be administered every other month, it will start as soon as the COVID-19 restrictions for fieldwork are lifted. The data collected from these shadowing visits are meant to triangulate and validate the self-report time use surveys administered over the phone/in person. The time shadowing will be carried out by a trained enumerator accompanying the CHW during a workday (7am to 6 pm).

#### Community surveys

Surveys will be conducted with two key informants (e.g. mayor, community chief, teachers, doctor, religious leaders, etc.) in each community on a monthly basis to obtain information about key community infrastructure, ongoing programs and events, the frequency and duration of local economic/weather/other shocks, and information on market access, and prices of key commodities. Key informants are identified by the CHWs in collaboration with the supervisors. Data collected from these surveys will be used to control for community-level time-varying socio-economic shocks during the study period that may affect our key outcomes of interest.

#### Administrative monitoring data

The main data source for caregiver-child dyad participation and engagement at the community health center will be administrative data from a digital tool used to monitor health and nutrition program activities (CommCare application) as part of their monitoring information system. Individual data on participation in program activities are collected by the CHWs on a paper monitoring registry, as well as an ECD-specific monthly monitoring registry. The NGO supervisors during one of the monthly visits to the community, enters the individual participation data contained in the registries into the CommCare application using the unique caregiver-dyad identification number provided by the census.

### Outcomes

The following primary and secondary outcomes will be collected:•*CHW time allocation* (Primary outcome), measured through a 24-h recall of time spent on program related tasks (group nutrition sessions, home visits, treatment of illnesses, administrative tasks, ECD group sessions, and toy maintenance), household chores, productive activities, caregiving and rest/social activities. This will be measured at baseline and monthly for 12 months through phone-surveys.•*CHW psychosocial wellbeing* (Secondary outcome), measured through the monthly phone surveys. Motivation and depression will be measured at baseline and every four months using the short-form Center for Epidemological Studies Depression Scale (CES-D) [23] and motivation scales [24] adapted to the Malagasy context and the Rosenberg Self-Esteem Scale [25]. Perceived stress will be measured monthly using the Perceived Stress 7-Item Scale (PSS-7) [26].•*Caregiver-child dyad participation in health and nutrition activities* (Primary outcome), measured through the administrative data monthly. The range of program activities that are collected range from monthly attendance to group promotion sessions and growth monitoring sessions, indicators of whether they received home visit in last month, and whether they received vitamin A supplementation, deworming and vaccinations (age-specific).•*Caregiver-child dyad participation in ECD sessions* (Primary outcome), measured through the administrative data monthly. Information ranges from number of ECD sessions attended by caregiver-child dyad in last month and whether the children transitioned from one age group to the subsequent one.

### Power calculations

#### CHW time allocation

We assumed repeated observations (baseline and 11 post implementation), with an auto-correlation coefficient of 0.7 (high) or 0.5 (low) for the correlation between follow-up measurements of CHW time allocation. We will control for baseline outcomes with an ANCOVA specification. We adjusted for the clustering design effect on sample size with an adjustment of (1 + ρ(m—1)), where ρ is the intra-cluster correlation (ICC) and m = 2 CHW within community or cluster. We assume an ICC of 0.2 and 0.3 on the activities performed by CHWs within a cluster, where an ICC = 0.2 is benchmarked on previous MAHAY CHW outcomes [27].

Using Stata Corp sampsi command, we performed sample size calculations with 80% power for an expected effect size of 0.5 SD in a bivariate comparison. A conservative sample size is 25 clusters per study arm (Table 1).

**Table 1 Tab1:** Sample size calculations: number of clusters per study arm

	Autocorrelation coefficient	
	High (0.7)	Low (0.5)
ICC = 0	15	19
ICC = 0.2	18	23
ICC = 0.3	20	25

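### Table 1 counts community health workers per arm but labels them clusters, so the stated requirement of 25 clusters per arm is about twice what its inputs imply

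*Protocol article*

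**What the plan says.** The CHW time allocation part of Power calculations gives these inputs: "We assumed repeated observations (baseline and 11 post implementation), with an auto-correlation coefficient of 0.7 (high) or 0.5 (low" for the correlation between follow-up measurements, baseline adjustment by ANCOVA, a design effect of 1 + ICC(m − 1) with m = 2 CHWs per community, and ICCs of 0.2 and 0.3. The target is stated as "we performed sample size calculations with 80% power for an expected effect size of 0.5 SD in a bivariate comparison". The result is captioned "Sample size calculations: number of clusters per study arm":

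| | r = 0.7 | r = 0.5 |
|---|---|---|
| ICC = 0 | 15 | 19 |
| ICC = 0.2 | 18 | 23 |
| ICC = 0.3 | 20 | 25 |

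The text concludes: "A conservative sample size is 25 clusters per study arm (Table 1".

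The data collection section confirms the cluster size: "Phone surveys will be conducted at baseline and monthly with 150 CHWs (two for each of the 75 study communities". Twenty-five communities per arm therefore supply 50 CHWs per arm.

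**The concern.** A design effect of 1 + ICC(m − 1) inflates a number of individuals. To express the result as clusters, it must then be divided by m. The ICC = 0 row suggests that this was not done. With no clustering and two CHWs per community, the number of communities should be about half the number of CHWs an individually randomised trial would need, yet 15 and 19 look like the individual numbers themselves.

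Whether the extra ECD work crowds out other CHW tasks is a central question of the trial. If the table is in the wrong unit, the protocol ties its sample size to the wrong detectable effect, and a null result on CHW time may be read against 0.5 SD when the design can detect a clearly smaller effect. The section on the T+ arm also refers to these power calculations when it justifies the six-month delay. Anyone who reuses Table 1 to plan a similar trial on the same assumptions would recruit about twice the clusters needed.

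**Working it through.** **Inputs from the article:** 80% power; difference 0.5 SD; one baseline and k = 11 follow-ups; r = 0.7 or 0.5; ICC 0, 0.2 or 0.3; m = 2.

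**Inputs assumed because the article does not state them:** two-sided 5% significance, and a baseline-to-follow-up correlation r₀ equal to r.

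**Step 1. Individuals per arm, single measurement.** 2(1.960 + 0.8416)² / 0.5² = 62.79.

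**Step 2. Repeated-measures ANCOVA factor,** (1 + (k − 1)r)/k − r₀²:
- r = r₀ = 0.7: 8/11 − 0.49 = 0.2373
- r = r₀ = 0.5: 6/11 − 0.25 = 0.2955

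**Step 3. Multiply by the design effect 1 + ICC, then round up. Last, divide the unrounded number by m = 2 and round up.**

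| ICC | r | CHWs per arm | Rounded up | Table 1 | Clusters per arm (÷ 2) |
|---|---|---|---|---|---|
| 0 | 0.7 | 14.90 | 15 | 15 | 8 |
| 0 | 0.5 | 18.55 | 19 | 19 | 10 |
| 0.2 | 0.7 | 17.88 | 18 | 18 | 9 |
| 0.2 | 0.5 | 22.26 | 23 | 23 | 12 |
| 0.3 | 0.7 | 19.37 | 20 | 20 | 10 |
| 0.3 | 0.5 | 24.12 | 25 | 25 | 13 |

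All six cells match, in units of CHWs. With r₀ = r, no variant tried gives the table as clusters: follow-up means only, change scores, 12 follow-ups, one-sided 5%, or 90% power.

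**Step 4. Could the r = 0.5 column be clusters under some other baseline correlation?** The requirement is largest when the baseline gives no information (r₀ = 0), where the factor is 6/11 = 0.5455. That needs 34.25, 41.10 and 44.52 CHWs for ICC 0, 0.2 and 0.3, which is 18, 21 and 23 clusters. The table shows 19, 23 and 25. With these inputs, no baseline correlation produces that column as clusters.

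**Step 5. What 25 communities × 2 CHWs per arm deliver.** The standard error in SD units is √(2 × factor × (1 + ICC)/50).
- ICC 0.3, r = 0.5: √(2 × 0.2955 × 1.3/50) = 0.124. The detectable effect at 80% power is 2.80 × 0.124 = 0.347 SD (0.354 with t on 48 df). Power at 0.5 SD is 98.1% (97.7% with t).
- ICC 0.2, r = 0.7: the detectable effect is 0.299 SD.

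**Step 6. Sensitivity, r₀ below r** (r = 0.7 between follow-ups):
- r₀ = 0.5: factor 8/11 − 0.25 = 0.4773. At ICC 0.3 this needs 38.96 CHWs, or 20 clusters. The detectable effect with 50 CHWs is 0.44 SD.
- r₀ = 0.3: factor 8/11 − 0.09 = 0.6373. At ICC 0.2 this needs 48.02 CHWs, or 25 clusters (0.49 SD). At ICC 0.3 it needs 52.02 CHWs, or 27 clusters (0.51 SD).

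**Step 7. Fewer follow-ups for T+.** The empirical specification treats the T+ effect as a six-month average. With 6 or 5 follow-ups, r = r₀ = 0.5 and ICC 0.3, the detectable effect is 0.37 or 0.38 SD.

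**The case against.** The strongest objection is that the diagnosis depends on a correlation the article never states. It defines 0.7 and 0.5 only as the correlation between follow-ups. With 0.7 between follow-ups and 0.5 between baseline and follow-up, the requirement is 29.97, 35.96 and 38.96 CHWs. Halved and rounded up, that is 15, 18 and 20, so the whole r = 0.7 column can also be read as correctly labelled clusters. This is true, but the r = 0.5 column cannot be read that way under any baseline correlation (step 4). Only the CHW reading explains all six cells with one set of inputs.

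A second objection is that 25 clusters for 0.5 SD is about right if the baseline correlation is as low as 0.3 and the follow-up correlation is 0.7. That stands as a caution about the size of the margin: the 0.30 to 0.35 SD figures hold only where the two correlations are equal. It does not explain how the table was derived.

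A third is that a blanket claim of 0.35 SD ignores the later start of T+. That also stands, though on the section's own assumptions it moves the figure only to 0.37–0.38 SD.

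Finally, the error is in the safe direction on the stated inputs, no analysis changes, and a null result should be judged by its confidence interval. This limits the consequences, but the sample-size statement for a primary outcome is still wrong. Calling 25 conservative does not rescue it: the word refers to the least favourable ICC and correlation, not to the unit.

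**Conclusion.** The concern holds. Table 1 gives CHWs per arm under a caption that says clusters. On the section's own inputs, the cluster requirement is 8/10, 9/12 and 10/13 per arm, and the conservative figure is 13 rather than 25, an overstatement of about a factor of two. At 25 communities per arm, power for 0.5 SD is about 98% in the least favourable cell, and the effect detectable with 80% power is about 0.30 to 0.35 SD over ICC 0.2–0.3.

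This rests on two-sided 5% and equal baseline and follow-up correlations. The match in all six cells supports both, but a reader needs to see them stated because the margin depends heavily on the second. The 75-community design is not undermined, and the separate calculation for caregiver-child participation, which uses 25 against 25 communities, is unaffected.

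**What to change.** - Relabel Table 1 as CHWs per arm, or halve it to 8/10, 9/12 and 10/13 clusters per arm, and correct the sentence that concludes 25 clusters.
- State what the design delivers: 25 communities with two CHWs each per arm give 80% power for about 0.35 SD at ICC 0.3 and r = 0.5, for T against control with 11 follow-ups. Give the T+ comparison its own figure (about 0.37–0.38 SD with 6 or 5 follow-ups on the same assumptions).
- State the significance level and the baseline-to-follow-up correlation used, and show a lower value as sensitivity. For example, a baseline correlation of 0.3 with r = 0.7 and ICC 0.3 gives 0.51 SD.

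The cost is a correction to one table and a few sentences. Sample size, allocation, data collection and analysis model stay as they are.

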#### Caregiver-child dyad participation/take up

Assuming participation comparisons between a minimum of 25 treatment and 25 control communities (50 clusters), we modeled the minimum detectable effect (MDE) size using the software package, Optimal Design (OD) Plus Version 3.01, for clustered randomized trials with repeated measures. We will have administrative data for 40 eligible caregiver-child dyads per community participating in the MCH&N programs at each of 12 time points. We assume an ICC ranging from 0.1 to 0.3 for participation of caregiver-child dyads in activities. Under these assumptions, we are powered for MDEs ranging between 0.31 SD (ICC = 0.1) and 0.47 SD (ICC = 0.3).

### Sampling, stratification and randomization

In order to capture efficiency gains from adjusting from observable differences in the design of the randomized experiment, we conducted stratified sampling [28]. We partitioned the covariate space into 16 strata, with stratification criteria that included region (Amoron’i Mania and Haute Matsiatra), remoteness of the community (above/below the median Euclidean distance to the closest health center), population size of the catchment area (above/below median number of children in the 6–30 months old age range), and CHW education level (above/below secondary level of educational attainment).

Within each of the 16 strata, we sampled six or 12 communities (one sextuplet drawn from each of seven smaller strata and two sextuplets drawn from each of nine large strata) to create a set of 25 sextuplets that are comparable along the stratification dimensions. Next, we randomly drew three communities selected from each sextuplet and allocated each to one of three possible arms (i.e. allocation ration of 1:1:1 in two treatment arms and one control arm) for a total of 75 communities in the final sample. This sampling approach ensures that each community has a cluster of comparable communities within its assigned stratum and allows for up to three back up communities for the potential need for replacement in case of refusal or drop-out by participating communities [28, 29]. All sampling and randomization were done by key research personnel using standard and reproducible computer-assisted software packages in Stata 16.

The random generation sequence and the random assignment of (i) communities to treatment arms and of (ii) households in case of over-subscription in T and T + will be performed by the research team. Due to the nature of the interventions, it is impossible to blind participants to their intervention group assignment. Interviewers will not be blinded as they will ask participants about their program-related experiences. However, the data will be masked to group assignment during the data analysis phase to blind the data analysts.

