#### Empirical specification

We have two primary estimating equations, which we discuss below. The first (Eq. 4) is our main specification for comparisons between each intervention arm and the control group (Primary Questions 1 & 2, Secondary Question 1). These models will be used to estimate the impact on CHW outcomes (time use and motivation) and caregiver-child dyad outcomes (participation and engagement). All specifications will control for the method of randomization by including strata indicator variables, month fixed effects to account for time-varying unobservable (to the researcher) factors, and correcting standard errors for clustering at the community level. For clarity, we reproduce one set of equations here, but they can be applied to either CHW-level or caregiver-child dyad-level analysis.

Let the outcomes of interest will be represented by $${Y}_{ijt}$$, where the subscript refers to CHW (or caregiver-child dyad) *i*, in community *j*, at time *t*.

The main ITT impact of each intervention arm on the outcome of interest is estimated as follows:4$${Y}_{ijt} = \alpha + {\beta }_{1}{T}_{j} +{\beta }_{2} {{T}_{+}}_{j}+ \gamma {Y}_{ij0} + {\delta }_{1}{X}_{ijt}+ {\delta }_{2}{V}_{jt}+ {\theta }_{s}+ {\lambda }_{t} + {\varepsilon }_{ijt}$$

where $${T}_{j}$$ or $${{T}_{+}}_{j}$$ are indicators for the random assignment of community j to treatment, $${Y}_{ij0}$$ are baseline outcomes for CHW (or caregiver-child dyad) i (ANCOVA specification), $${X}_{ijt}$$ are CHW-level (or caregiver-child level) covariates (e.g. age, gender, education level), are $${V}_{jt}$$ are time-varying community-level characteristics (e.g. shocks, prices/wages), $${\theta }_{s}$$ are strata fixed effects (randomization triplet fixed effects), $${\lambda }_{t}$$ is a set of month fixed-effects, and $${\varepsilon }_{ijt}$$ are error terms clustered at the community level.

β_1_ and β_2_ represent the average impact of being assigned to T or T + over 12- and 6-month periods, respectively, relative to the control group. Testing primary question 1 and primary question 2 is equivalent to testing whether (H0: β_1_ = 0 and (H0: β_2_ = 0).

To address Primary Question 3, we restrict the sample to the communities that are offered any ECD intervention (T or T +) and estimate the following equation:5$${Y}_{ijt} = \alpha + {\beta }_{2} {{T}_{+}}_{j}+ \gamma {Y}_{ij0} + {\delta }_{1}{X}_{ijt}+ {\delta }_{2}{V}_{jt}+ {\theta }_{s}+ {\lambda }_{t}+ {\varepsilon }_{ijt}$$

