These analyses will occur in a restricted sample of only communities where T = 1 or T + = 1. Here, testing (H0: β_2_ = 0) allows to test whether being assigned T + provides any additional benefit over and above T.

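### Analysts cannot be blind to control versus ECD once they handle task-level CHW time, ECD attendance, or the restricted and pooled-arm analyses, so the unqualified blinding statement needs narrowing

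*Protocol article*

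**What the plan says.** All references are to the protocol article.

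- **Sampling, stratification and randomization.** Participants and interviewers cannot be blinded. By contrast, "the data will be masked to group assignment during the data analysis phase to blind the data analysts". No method, code holder or limit by outcome is given. On allocation, the section says that the random assignment of communities and of "households in case of over-subscription in T and T + will be performed by the research team".
- **Outcomes.** CHW time allocation (primary) is a 24-hour recall by task, including "administrative tasks, ECD group sessions, and toy maintenance". Participation in ECD sessions (primary) includes the "number of ECD sessions attended by caregiver-child dyad in last month". Participation in health and nutrition activities (primary) includes "monthly attendance to group promotion sessions and growth monitoring sessions".
- **Administrative monitoring data.** CHWs keep a general registry "as well as an ECD-specific monthly monitoring registry". Both are entered in CommCare under the dyad's census identifier.
- **Empirical specification.** Eq. 4 compares each ECD arm with control. For Eq. 5 (Primary Question 3): "These analyses will occur in a restricted sample of only communities where T = 1 or T + = 1".
- **Subgroup analyses.** Heterogeneity is estimated with the two treatment arms pooled, and machine-learning methods will be explored.

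**The concern.** Replacing arm names with codes does not help when the data contain a quantity that is zero by design in one arm. Control communities hold no ECD sessions, so time on sessions and attendance at them separate control from ECD whatever the arms are called. Two specified analyses also require the control group to be known: one removes it, and the other sets it against the two ECD arms combined.

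Analysts are the only level at which the article claims blinding, and CHW time is self-reported by unblinded workers to unblinded interviewers. In the article several analysis choices are described by type or example rather than closed: the covariates used against chance imbalance, the make-up of the participation index, the moderators, and the machine-learning work. If these are settled after the analyst can see which communities are controls, a trial report repeating the sentence would claim a safeguard that was absent for that contrast.

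**Working it through.** The blinding statement carries no figure to reproduce. The check sets it against each analysis, then asks how much the recall data reveal by themselves.

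**1. What each analysis lets the analyst see**

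| Analysis | What the analyst must handle | Control v ECD maskable? | T v T+ maskable? |
|---|---|---|---|
| CHW time by task, Eq. 4 | ECD-session time, absent by design in control | No | Yes, with codes |
| ECD participation, Eq. 5 | Attendance that exists only in T and T+; controls removed | No | Yes, with A/B codes |
| Health and nutrition participation, Eq. 4 | Activities offered in all three arms | Yes, if kept apart from ECD variables | Yes |
| Moderators of health and nutrition participation | T and T+ pooled against control | No | Arms are merged |
| CHW psychosocial scales, Eq. 4 | No arm-specific items described | Yes, if kept apart from ECD variables | Yes |

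A ready-made pooled variable would not rescue the fourth row: it would have 25 + 25 = 50 communities against 25, so group size alone identifies control.

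**2. How much the recall data reveal without the attendance file**

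Inputs from the article: two CHWs per community and 11 post-baseline recalls (Power calculations); 25 communities per arm; four age groups with fortnightly sessions (ECD group sessions). That gives 4 × 2 = 8 sessions per community in about 30 days.

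Assumption: the article does not say how sessions are shared between the CHWs, so the share *p* of recall days with ECD work is varied, and recalls are treated as independent.

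- One community shows no ECD time: (1 − *p*)^(2 × 11) = (1 − *p*)^22
- A whole arm shows none: (1 − *p*)^(22 × 25)

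| Assumed sharing | *p* | One community shows none | Arm of 25 shows none |
|---|---|---|---|
| Both CHWs at all 8 sessions, one a day | 8/30 = 0.27 | 0.1% | 8 × 10⁻⁷⁵ |
| Sessions split between CHWs | 4/30 = 0.13 | 4% | 7 × 10⁻³⁵ |
| Split, two sessions a day | 2/30 = 0.07 | 22% | 3 × 10⁻¹⁷ |

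At arm level, the control code is recognisable with practical certainty in every case. For a single community the recall alone can miss ECD status; the ECD attendance file would largely close that gap.

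**3. T versus T+**

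No listed primary outcome necessarily separates these arms. Session play materials are used in both, and the tool for tracking toy inventory is described for the common ECD programme. In Eq. 5, swapping the codes turns β₂ into −β₂ and leaves its standard error and p-value unchanged, so the model can be fitted blind. Eq. 4 as printed treats the two indicators alike. However, its coefficients are read over 12 and 6 months, so any coding of those periods would need the T+ label.

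**The case against.** The strongest reply is that the sentence speaks of masking the data, not only the arm label, and that a journal article may leave the procedure to the full protocol or analysis plan. That stands as far as the missing procedure goes: its absence is not the finding. But no procedure lets an analyst estimate time on ECD sessions, fit the restricted model or pool the arms without learning which communities are controls.

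Second, the leak does less damage than it may seem. ECD participation is compared only between T and T+, and recognising controls reveals nothing about that contrast. This stands. It leaves CHW time allocation as the primary outcome where the tested contrast is itself exposed.

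Third, much is already fixed: intention to treat, ANCOVA on baseline, triplet and month fixed effects, community-clustered errors and the coefficients to be tested. Covariates and moderators are illustrated. This stands too, so masking is not the only protection.

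A reader might infer three stronger things that the article does not support:

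- **That masking is worthless throughout.** Health and nutrition participation and the psychosocial scales do not reveal the arm by themselves, and T versus T+ can be coded.
- **That the same people allocate and analyse.** The research team allocates and also receives the data for analysis, but the article does not say which members do which. The separately stored key under Data management concerns subject identifiers, so it settles nothing about arm.
- **That the protocol offers masking as protection for discretionary choices.** It states no purpose beyond blinding the analysts; the link to open choices is an inference, though a reasonable one.

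**Conclusion.** The statement is wrong as written, to a limited extent. Blinding to control versus ECD cannot hold for the data of two of the three primary outcomes (CHW time by task and ECD attendance), for Eq. 5, or for the pooled-arm heterogeneity analysis. Among the primary contrasts, the practical exposure is mainly ECD versus control on CHW time. Masking remains achievable elsewhere, given separation of files and coded labels.

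No estimand, sample size or error rate changes, and no bias has been quantified. The consequence is a claimed safeguard that would be misreported for this contrast, with some analysis choices open in the article. The conclusion that outcomes reveal control versus ECD rests on the design itself. Only the probabilities depend on the assumed session sharing and on independent recalls.

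**What to change.** 1. Limit the sentence to what can be masked: health and nutrition participation and the psychosocial scales while held apart from ECD variables, and T versus T+ under codes.
2. Before the allocation is released, fix the covariate list, participation index, moderators and analysis code. Do this on data with arm labels permuted within triplets, ECD attendance withheld, and ECD-session and toy-maintenance time collapsed into total programme time.
3. Run Primary Question 3 with T and T+ as A/B codes, the code being held by a team member who is not doing the analysis.
4. State that after release the analysts are not blind to control versus ECD.

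The cost is a short data-preparation step and some wording in the protocol or analysis plan. No new data or participants are needed. The downside is a less favourable blinding claim.
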